### Intervention: the BRIDGES HIV doula program

2.5

The BRIDGES intervention pairs each enrolled mother–infant dyad with an HIV-trained doula (study team personnel) who provides the following services from enrollment during pregnancy through 12 weeks postpartum:
Prenatal education on infant feeding options (breastfeeding, formula, banked donor milk), consistent with the shared decision-making framework recommended by U.S. Perinatal Guidelines (10, 11)ART adherence support, including medication reminders, barrier identification, and problem-solvingAppointment adherence support to ensure attendance at prenatal, postnatal, and pediatric visitsLactation counseling and support for mothers who elect to breastfeed, including education on exclusive breastfeeding recommendations, breast health monitoring, and weaning guidanceGuidance on adherence protocols specific to infant feeding choice, including infant ARV prophylaxis schedules and maternal/infant viral load monitoringThe doula will meet with mothers and their babies during regularly scheduled prenatal, postnatal, and pediatric visits, either before or after the scheduled clinical visit either in person or remotely. Each visit will take up to 60 min. Postnatally, mothers and infants will meet with the doula at each postnatal visit (one or two) and every 4 weeks for 12 weeks.

The clinical monitoring schedule for HIV-exposed mother–infant dyads below follows guideline-based care; the doula-mediated education, adherence support, and care coordination delivered through BRIDGES are not standard of care and represent the adapted, novel component of the intervention.

Clinical monitoring protocols are differentiated by feeding choice. For mothers who initiate breastfeeding: mothers will continue ART throughout breastfeeding, with the goal of maintaining HIV viral load < 50 copies/mL; infants will receive ARV prophylaxis until weaned off breast milk; maternal HIV viral load will be monitored monthly for up to 3 months or until the infant is weaned, consistent with the guideline recommendation of monitoring every 1–2 months; infant HIV nucleic acid testing will follow the schedule recommended by the AAP (at 14–21 days, 1–2 months, 4–6 months, every 2 months during lactation, and at 4–6 weeks and 3 and 6 months after weaning); breastfeeding will be temporarily interrupted or discontinued if maternal viral load becomes detectable, particularly if ≥200 copies/mL; and the doula will educate on and monitor for breastfeeding complications (mastitis, cracked/bleeding nipples, infant thrush) that may warrant temporary breastfeeding interruption (6, 7, 10, 11). For mothers who elect to formula feed: standard of care will be followed, with infant ARV prophylaxis for 4 weeks and viral load measured at birth, 2 weeks, and 4 weeks.

For mothers who breastfeed, expressed-milk pumping and pasteurization (including exclusive pumping) will be offered as a supported option during viral blips, mastitis, or other periods of increased transmission risk for those who prefer not to introduce formula. Infant antiretroviral prophylaxis will be provided for the duration of breastfeeding per site protocol, and banked donor milk (including use as a supplement to the mother's own milk) will be supported, with data collected on source and frequency of use. Specific infant ARV regimen and prophylaxis decisions will follow the treating clinical team's guidance and institutional protocol.

The clinical monitoring protocols follow guideline-based standard of care and are fixed; the doula-delivered intervention components (educational content, materials, and delivery approach) and recruitment procedures are co-developed and iteratively refined with the Advisory Group and clinical partners. The Advisory Group structure will be established within the existing Pediatric Community Advisory Board framework. Participants will be enrolled during pregnancy regardless of infant feeding intention, allowing the study to capture the full spectrum of infant feeding decisions and the doula's role in supporting each choice.

### Study procedures overview

2.6

Figure 1 summarizes the participant sequence from enrollment through 12 weeks postpartum. Eligible women are referred from the UM Women's HIV Clinic and enrolled during pregnancy at the UM CFAR Clinical Research Unit, where written informed consent and baseline data collection occur. From enrollment through 12 weeks postpartum, each mother–infant dyad is paired with an HIV-trained doula who provides feeding-options education, ART and appointment adherence support, and lactation counseling, in person or via Zoom for Healthcare. After delivery, clinical monitoring follows the mother's infant-feeding choice (breastfeeding/expressed milk versus formula), using the guideline-based schedules described in Section 2.5. Participants complete up to three research visits for questionnaire and medical-record data collection, with postnatal doula contact at each postnatal visit and every four weeks through week 12, and a 30-minute individual interview at study exit (approximately 12 weeks postpartum).

**Figure 1 F1:**
[figure not shown]
BRIDGES study schema: participant timeline from enrollment through 12 weeks postpartum.

### Data collection

2.7

All quantitative questionnaires will be available in English, Spanish, and Haitian Creole. These include:
Sociodemographic Questionnaire: Gathers data on participants' sociodemographic information (age, race/ethnicity, education, income, insurance status, language), overall health, and pregnancy-related factors.HIV Health-Related Data: Self-reported items on overall health and HIV history (collected by questionnaire).Medical Record Data: Extracted from the electronic medical record (not by questionnaire): CD4 count, viral load history, ART regimen and duration, and attendance at prenatal, postnatal, and pediatric visits.Obstetrical History: Gravidity, parity, prior infant feeding experiences.Substance Use and Mental Health History: Including screening for postpartum depression using the Edinburgh Postnatal Depression Scale (EPDS), which occurs more frequently in individuals with HIV compared to those without HIV (10, 11).Psychosocial Measures: HIV stigma measured with the 40-item HIV Stigma Scale (HSS) (26), medical mistrust measured with the 12-item Group-Based Medical Mistrust Scale (GBMMS) (27), and resilience measured with the 25-item Connor-Davidson Resilience Scale (CD-RISC-25) (28).Engagement with External Resources: Use of and referral to external support services, including the Special Supplemental Nutrition Program for Women, Infants, and Children (WIC), lactation consultation, food assistance, housing, and transportation services, will be documented at each doula visit to characterize the broader support context surrounding each dyad.Infant Feeding Outcomes: Feeding method chosen, duration of breastfeeding if applicable, breastfeeding complications, and, for participants using banked donor milk, the source, frequency, and whether donor milk is used exclusively or as a supplement to the mother's own milk.ART Adherence Measures: ART adherence will be assessed using the 3-item self-report adherence measure (Wilson et al.) (29), a 30-day count of days with a missed dose plus self-ratings of how well and how often medications were taken as prescribed, together with maternal HIV viral load from the electronic medical record as a biological marker of sustained adherence.Maternal and Infant HIV Viral Load Results and Infant HIV Testing Results.Doula Visit Attendance and Engagement: Visit engagement will be operationalized as the proportion of scheduled doula visits attended (number of completed visits divided by the number scheduled per the protocol), the proportion of recommended prenatal, postnatal, and pediatric clinical visits attended, and doula-documented participation during each contact. These attendance and engagement metrics constitute the primary feasibility outcomes.Participant Satisfaction: Participant satisfaction will be assessed using a brief validated instrument, the Client Satisfaction Questionnaire (CSQ-8), administered at study completion to complement the qualitative interviews.In addition to doula visits, participants will meet with research staff for up to 3 additional study visits at the UM CFAR Clinical Research Unit for data collection.

Qualitative data collection includes individual interviews. After completing visits with the doula (up to 12 weeks postpartum), patient participants will be invited to participate in a 30-minute individual interview to share their experiences with the BRIDGES study. Interviews will be conducted at the UM CFAR Research Unit or via Zoom for Healthcare. A semi-structured interview guide will explore experiences with the doula intervention, perceived impact on infant feeding decision-making and confidence, barriers and facilitators to ART adherence during the perinatal period, experiences with breastfeeding complications (if applicable), and suggestions for intervention improvement. To ensure data sources are not conflated, participant interviews (Aim 2) will use an individual format; group formats are reserved for the Advisory Group (Aim 1).

During Advisory Group meetings (Aim 1), individual and group interview data will be gathered using semi-structured guides. Data will inform the adaptation and refinement of the BRIDGES intervention.

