### Outcomes

2.9

As an exploratory pilot/feasibility study, the primary outcomes are feasibility and acceptability.

Primary outcomes include recruitment and retention rates, intervention completion rate and doula visit attendance; participant-reported experiences and acceptability (qualitative interviews and, if adopted, a satisfaction survey); and ART adherence and maintenance of viral suppression. Clinical and psychosocial measures are framed as exploratory signal-detection outcomes to inform a future multi-site trial (Aim 3).

Secondary outcomes include infant feeding method chosen and duration; breastfeeding complications (mastitis, cracked nipples, infant thrush, low milk supply); infant HIV testing completion and results; postpartum visit attendance; and changes in psychosocial measures (HIV stigma, medical mistrust, resilience).

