### Data analysis

2.10

**Quantitative analysis:** Descriptive statistics will characterize the study sample and summarize clinical outcomes. Metrics will include recruitment rate, retention rate, doula visit attendance, and intervention completion, with confidence intervals reported around key feasibility proportions (e.g., retention). As a pilot, the sample size (*N* = 15) is based on feasibility and resource considerations rather than a formal power calculation. Within-participant change over the study period (e.g., maintenance of viral suppression across pregnancy and the postpartum period, breastfeeding duration for those who elect to breastfeed, and infant HIV testing completion) will be summarized descriptively. Because this is a single-arm pilot without a control group, no between-group effect estimation or controlled pre-post inference is implied.

**Qualitative analysis:** Audio-recorded interviews will be transcribed and analyzed using thematic analysis with password-protected, cloud-based qualitative data processing systems (Dedoose). Analysis will employ line-by-line coding, constant comparison, and axial coding to identify central themes. CFIR constructs will be used as a deductive coding framework to evaluate implementation determinants (23, 24), supplemented by inductive codes emerging from the data. If both individual and group interviews are retained for participants (pending the decision in Section 2.6), they will be analyzed as separate data sources rather than pooled.

**Mixed-methods integration:** Quantitative and qualitative findings will be integrated using a convergent design, with results triangulated to provide a comprehensive understanding of intervention acceptability and preliminary effectiveness. Qualitative data from both Aim 1 (Advisory Group) and Aim 2 (participant interviews) will be used to refine the BRIDGES intervention for future testing.

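### Acceptability, a primary outcome, is measured at the end of the programme, so it leans towards completers, and the text conflicts on the CSQ-8 and on participant group interviews

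*Protocol article*

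**What the plan says.** Section 2.9 (Outcomes) states: "As an exploratory pilot/feasibility study, the primary outcomes are feasibility and acceptability". It then lists the sources of the acceptability outcome: "participant-reported experiences and acceptability (qualitative interviews and, if adopted, a satisfaction survey".

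On timing, Section 2.7 (Data collection) says of the interview: "After completing visits with the doula (up to 12 weeks postpartum), patient participants will be invited to participate in a 30-minute individual interview". Section 2.6 places the same interview at study exit, at roughly 12 weeks postpartum. On the questionnaire, Section 2.7 says: "Participant satisfaction will be assessed using a brief validated instrument, the Client Satisfaction Questionnaire (CSQ-8), administered at study completion".

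On interview format, Section 2.7 says: "participant interviews (Aim 2) will use an individual format; group formats are reserved for the Advisory Group (Aim 1"). Section 2.10 (Data analysis) begins a sentence with: "If both individual and group interviews are retained for participants (pending the decision in Section 2.6"). It goes on to say that the two formats would be analysed separately.

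**The concern.** There are two linked problems.

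The first is timing. Both acceptability sources are scheduled for women who have reached the end of the doula visits or of the study. A woman who finds the programme intrusive, unhelpful or hard to fit into her life is plausibly more likely to stop before then. If data are gathered only at the stated times, the acceptability result leans towards those who stayed. The interviews also supply the participant material for the CFIR coding of implementation determinants, and the Discussion relies on that qualitative material to offset the small sample. Barriers that lead women to leave are among the most useful things a pilot can learn before a multi-site trial.

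The second is that the instruments are not settled. The CSQ-8 is the only quantitative acceptability measure the article describes. One section commits to it, while the section that defines the primary outcomes makes it optional. The format of the participant interviews is fixed in one section and open in another.

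**Working it through.** The plan states no acceptability figure, so there is nothing to reproduce. The check is a comparison of the text, followed by an illustration on assumed dropout.

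**Timing**

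| Source | Section | Stated time |
|---|---|---|
| Interview | 2.7 | after the doula visits are completed |
| Interview | 2.6 | study exit, about 12 weeks postpartum |
| CSQ-8 | 2.7 | study completion |

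The article describes no earlier collection of either source. The plan itself allows for non-completion: retention and intervention completion are primary outcomes (Section 2.9), and women may withdraw at any time (Section 4.4).

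**Contradictions**

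| Item | One section | Another section |
|---|---|---|
| CSQ-8 | 2.7: will be used | 2.9: only if adopted |
| Group interviews, Aim 2 participants | 2.7: individual format only | 2.10: open, pending a decision in 2.6 |

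Section 2.6 mentions only a 30-minute individual interview. It records no decision on format, taken or pending, so the cross-reference leads nowhere.

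**Illustration of size**

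Inputs: n = 15 enrolled (Section 2.4). The number of leavers d is an assumption, because the article gives no dropout rate. A satisfied/not satisfied split is also an assumption, because the article defines none.

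Let m = n − d women respond and s of them be satisfied.

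- Proportion among completers: s/m.
- Range for all enrolled: from s/n (no leaver satisfied) to (s + d)/n (every leaver satisfied).
- Width of that range: d/n, whatever the value of s.
- Exact (Clopper-Pearson) lower 95% limit when s = m: 0.025^(1/m).

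With every completer satisfied (s = m):

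| d | Completers (exact 95% CI) | All 15, lowest to highest | Width |
|---|---|---|---|
| 1 | 14/14 = 100% (76.8 to 100) | 14/15 = 93.3% to 100% | 6.7 points |
| 3 | 12/12 = 100% (73.5 to 100) | 12/15 = 80.0% to 100% | 20.0 points |
| 5 | 10/10 = 100% (69.2 to 100) | 10/15 = 66.7% to 100% | 33.3 points |

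For d = 3, the exact 95% CI around the lowest value, 12/15, is 51.9% to 95.7%.

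The confidence interval among completers describes sampling error in completers. It does not cover the uncertainty about women who gave no answer.

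**The case against.** A reader might infer that acceptability is collected only from women who finish. The documents do not say so. No section excludes early leavers. The phrase study exit could include an early exit, although Section 2.6 ties it to about 12 weeks. What happens at withdrawal is the kind of detail a journal article leaves to the full protocol. This stands, so the point rests on the stated timing and not on a missing procedure.

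A reader might also take the gap between 100% and 80% as the expected bias. It is not. The dropout, the unanimous satisfaction of completers and the dissatisfaction of every leaver are all assumed. The plan defines no satisfaction cut-off, and Section 2.10 promises intervals for key feasibility proportions, with retention as its example, not for satisfaction. Acceptability here is largely qualitative.

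Disengagement would not be invisible either. Retention, completion and attendance are reported alongside acceptability, and the doula records participation at each contact. That shows how many women left, but not what they thought of the programme. Aim 1 Advisory Group data add some information on barriers, but not from the women who received the intervention and stopped.

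Finally, it would be wrong to conclude that group interviews as a whole are in doubt. Section 2.7 plans them for the Advisory Group. Only Aim 2 participants are affected, and the individual interview is never in question. Section 2.10 would also keep the two formats separate in analysis, so this conflict is mainly one of wording.

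None of this removes the two contradictions. They lie in the current text, and a fuller protocol would not reconcile these sections with each other.

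**Conclusion.** The point holds in a limited form. Both acceptability sources are timed to the end of the programme and, followed as written, this tends to leave out women who stop early. The likely direction is favourable, on the assumption that leavers are on average less satisfied than completers. The size cannot be derived from the article. The illustration shows only that each woman who gives no answer widens the range of possible values by 1/15, or 6.7 percentage points.

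The two contradictions are certain and need no assumption. The conflict over the CSQ-8 matters more, because it leaves open whether the only quantitative acceptability measure is part of a primary outcome. The conflict over group interviews is confined to Aim 2 participants. The sponsor should address all of this, because acceptability is a primary outcome meant to inform a later multi-site trial.

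**What to change.** - In Sections 2.6 and 2.7, state that the interview and the CSQ-8 are offered to every enrolled woman at study exit, or at her last contact if she withdraws or stops attending. This can be in person or by Zoom, which Sections 2.3 and 2.7 already allow for study procedures and interviews.
- In Section 2.10, state that CSQ-8 scores will be reported with the number responding out of all enrolled, and that non-responders will be described, for example by visits attended and time of leaving. No satisfaction cut-off is needed.
- In Section 2.9, remove the condition on the satisfaction survey so that it agrees with the commitment to the CSQ-8 in Section 2.7.
- In Section 2.10, delete the conditional sentence on participant group interviews together with its pointer to Section 2.6.

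The cost is a few extra contacts and some wording edits. Some women who leave will decline, so the gap will be reduced and made visible but not closed. The acceptability result may also be less favourable.

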### Recruitment and enrollment

2.8

UM HIV providers (non-study team members) will be made aware of the study during weekly meetings and grand rounds and will be given information to share with their patients to contact the clinical research team located in the UM CFAR Clinical Research Unit. Participants will be referred from the UM Women's HIV Clinic to the UM CFAR Clinical Research Unit, where enrollment activities will take place. Medical records may be reviewed for inclusion/exclusion criteria. The study will be open to all women who are referred, regardless of infant feeding intention (e.g., breastfeeding, formula feeding). The primary sources of referral will be University of Miami HIV care providers listed on the protocol as study team members.

Upon confirming eligibility, participants will undergo the consent process and be enrolled. Written consent will be obtained in a private room at the UM CFAR Clinical Research Unit. The research assistant will inform the women of the study's purpose and protocol and read the informed consent, which outlines all aspects of the study. If a participant wants to discuss participation with family members, the research assistant will schedule another appointment. Consent will be obtained in English, Spanish, and Haitian Creole.

Advisory Board members will be recruited from the Pediatric HIV Community Advisory Board and will provide verbal consent at the first Advisory meeting.

### Outcomes

2.9

As an exploratory pilot/feasibility study, the primary outcomes are feasibility and acceptability.

Primary outcomes include recruitment and retention rates, intervention completion rate and doula visit attendance; participant-reported experiences and acceptability (qualitative interviews and, if adopted, a satisfaction survey); and ART adherence and maintenance of viral suppression. Clinical and psychosocial measures are framed as exploratory signal-detection outcomes to inform a future multi-site trial (Aim 3).

Secondary outcomes include infant feeding method chosen and duration; breastfeeding complications (mastitis, cracked nipples, infant thrush, low milk supply); infant HIV testing completion and results; postpartum visit attendance; and changes in psychosocial measures (HIV stigma, medical mistrust, resilience).

### Data analysis

2.10

**Quantitative analysis:** Descriptive statistics will characterize the study sample and summarize clinical outcomes. Metrics will include recruitment rate, retention rate, doula visit attendance, and intervention completion, with confidence intervals reported around key feasibility proportions (e.g., retention). As a pilot, the sample size (*N* = 15) is based on feasibility and resource considerations rather than a formal power calculation. Within-participant change over the study period (e.g., maintenance of viral suppression across pregnancy and the postpartum period, breastfeeding duration for those who elect to breastfeed, and infant HIV testing completion) will be summarized descriptively. Because this is a single-arm pilot without a control group, no between-group effect estimation or controlled pre-post inference is implied.

**Qualitative analysis:** Audio-recorded interviews will be transcribed and analyzed using thematic analysis with password-protected, cloud-based qualitative data processing systems (Dedoose). Analysis will employ line-by-line coding, constant comparison, and axial coding to identify central themes. CFIR constructs will be used as a deductive coding framework to evaluate implementation determinants (23, 24), supplemented by inductive codes emerging from the data. If both individual and group interviews are retained for participants (pending the decision in Section 2.6), they will be analyzed as separate data sources rather than pooled.

**Mixed-methods integration:** Quantitative and qualitative findings will be integrated using a convergent design, with results triangulated to provide a comprehensive understanding of intervention acceptability and preliminary effectiveness. Qualitative data from both Aim 1 (Advisory Group) and Aim 2 (participant interviews) will be used to refine the BRIDGES intervention for future testing.

